**Figure 1 F1:**
[figure not shown]
**Flowchart of the TOROS study.** OSA: obstructive sleep apnea; CPAP: continuous positive airway pressure; TAU: treatment as usual.

The Medical Ethical Review Board of the Academic Medical Centre, Amsterdam, approved the study. The inclusion period started in October 2011. The study is registered at the Dutch trial register (http://www.trialregister.nl) and identified as NTR3412.

### Patient sample and procedures

This study is conducted in Heliomare rehabilitation center in the Netherlands. Annually, approximately 150 stroke patients are admitted to Heliomare. Neurologists or rehabilitation physicians of hospitals in the surrounding area refer patients. Patients with vascular dementia or comorbid neurodegenerative diseases (e.g., Alzheimer’s or Parkinson’s disease) are excluded from rehabilitation in Heliomare and are referred to the rehabilitation unit of a nursing home. The majority of the admitted patients are in the post-acute phase, i.e., on average, two to three weeks post-stroke. The average length of stay in Heliomare is nine weeks (standard deviation of four weeks). An earlier study showed that the prevalence of OSA in stroke patients admitted to Heliomare is around 50% [23]. At admission to the rehabilitation unit, stroke severity and functional dependence scales are used to determine the patient’s functional status. In the first week of hospitalization, patients are interviewed with a questionnaire to determine the presence of common symptoms of OSA. Subsequently, their oxygen desaturation index (ODI), defined as the mean number of desaturations of ≥3% from baseline per hour, is assessed with nocturnal pulse oximetry. Patients with an ODI of five or higher are further tested for OSA by polygraphy. Patients with an AHI of 15 or higher on polygraphy are diagnosed with OSA and patients with a normal ODI (<5) [23,24] or AHI below 15 are defined as non-OSA patients. Within four weeks of admission, a neuropsychological assessment is administered to determine the level of cognitive functioning. Stroke patients meeting the following inclusion criteria are invited to participate within six weeks from admission to Heliomare: [1] stroke confirmed by a neurologist, [2] age between 18 and 85 years, [3] admission to Heliomare between 1 and 16 weeks post-stroke, and [4] able to participate in the OSA screening and neuropsychological assessment. Exclusion criteria are: [1] severe unstable medical conditions, respiratory failure or history of severe congestive heart failure, [2] traumatic brain injury, [3] severe aphasia, confusion or psychiatric comorbidity, [4] central sleep apnea or previously diagnosed OSA. Patients with severe OSA (AHI >60 and oxygen desaturations below 70%), which could endanger the patient’s health if treatment is not immediately started, are excluded from the RCT part of the study. Before inclusion, patients give written informed consent.

### Randomization and blinding

Participants with OSA will be randomized immediately after the baseline assessments. The minimization technique [25] will be used to minimize imbalance between the treatment arms for age, severity of OSA, stroke subtype (ischemic or hemorrhage) and severity of cognitive impairment. Assessors of cognitive and functional outcome measures will be blinded to treatment allocation.

### Intervention

CPAP treatment is set up and monitored by a specialized ‘Respicare’ team. This team exists of two rehabilitation physicians, two nurse practitioners and four nurses working on the neurorehabilitation unit specialized in sleep and breathing disorders. Before treatment is initiated, a CPAP mask, connecting hose and CPAP device are set up for each patient. Different masks are used, from small nasal pillows to a full-face mask, depending on the patient’s preference. Personalized instructions are given by one of the Respicare team members and a written manual for the CPAP device is provided. If possible, the partner or a close relative is also provided with instructions on the use of the CPAP device. Patients are asked to wear the mask for a short period during the day to become accustomed to using the CPAP device. Within the first week, the CPAP treatment is evaluated together with the patient and CPAP titration is performed using pulse oximetry. The pressure is adjusted until the ODI is reduced to normal (ODI <5). If titration by nocturnal oximetry fails to adequately reduce the ODI, CPAP is titrated by polygraphy to reduce the AHI to <5 or to the highest pressure tolerated. The CPAP device is provided with a memory card to evaluate the effectiveness of CPAP therapy over time and to monitor CPAP compliance. The Respicare team has contact with the patients regularly during the intervention period to help troubleshoot problems and encourage compliance. Patients who are discharged during the four-week intervention period are followed-up by telephone.

### Primary outcomes

The primary outcome measures of this study are cognition and functional status. The following nine cognition domains are assessed: vigilance, attention, memory, working memory, executive functioning, language, visuoperception, psychomotor ability and intelligence. The neuropsychological test battery of standardized neuropsychological tests [26] is assessed by a trained psychological assistant. For a number of cognitive domains, non-verbal alternative tests are included for patients with aphasia. A language comprehension test is also included for aphasic patients. The obtained test scores are transformed into demographically corrected z-scores. In case of multiple tests within one domain, the average z-score for the domain is calculated. In Table 1 all tests are summarized by cognitive domain.

**Table 1 T1:** Neuropsychological tests by cognitive domain

** *Cognitive domain* **	** *Neuropsychological test* **
Vigilance	Psychomotor vigilance task
Attention	D-Kefs trail making test (TMT)
	*Color trails test
	d2 Test of attention
Memory	Rey’s auditory verbal learning test
	*Location learning test
Working Memory	WAIS-III letter-number sequencing
	*WMS-IV symbol span
Executive functioning	D-Kefs TMT letter-number switching
	Tower of London
Language	GIT-II category fluency
	**Token test
Visuoperception	D-Kefs TMT visual scanning
	Bells test
Psychomotor ability	D-Kefs TMT motor speed
	Finger tapping
Intelligence	WAIS-III matrix reasoning

*non-verbal alternative; **only administered in patients with aphasia.

Functional status is assessed by measures of neurological status and functional dependence. The rehabilitation physician administers two scales of neurological status, the Canadian Neurological Scale [27] and the National Institutes of Health Stroke Scale [28]. The obtained scores are transformed into z-scores and averaged into one score for neurological status. The nurse practitioner scores the level of functional dependence on the Utrecht Scale for Evaluation of Rehabilitation [29]. This scale can be converted to the Barthel Index [30].

### Secondary outcomes

Secondary outcome measures of the TOROS study are sleepiness (Stanford Sleepiness Scale), fatigue (Checklist Individual Strength), mood (Hospital Anxiety and Depression Scale), and subjective sleep quality (Sleep Quality Scale) [31-34]. A trained psychological assistant administers these measures after the neuropsychological assessment. The Utrecht Scale for Evaluation of Rehabilitation – Participation [35] is used to evaluate work, leisure and social activities at six months and one year after the inclusion. The patients complete this questionnaire at home.

Objective measurements of sleep are made using standardized pulse oximetry (WristOx®; Nonin Medical, Plymouth, USA) and ambulatory overnight cardiorespiratory polygraphy (Embletta®; Embla, Ottowa, Canada). The ODI (mean number of oxygen desaturations of ≥3% per hour) is calculated from the pulse oximetry data using automated analysis. Trained staff manually scores the polygraph recordings. Apnea is defined as a reduction of airflow of ≥90% for at least 10 seconds and hypopnea is defined as a reduction of airflow of ≥50% for at least 10 seconds followed by an oxygen desaturation of ≥3%. The AHI is defined as the mean number of apneas and hypopneas per hour in bed. The change of AHI measured by polygraphy and treatment compliance are used as moderating variables in the RCT.

A self-report questionnaire is administered to identify OSA symptoms (e.g., snoring, daytime sleepiness, morning headaches). Socio-demographic and clinical characteristics such as age, sex, education, body mass index (BMI), medication use and life style variables (e.g., smoking) are obtained from medical records.

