## Methods

### Design

In the RCT, 70 OSA patients will be randomized to receive four weeks of CPAP treatment or four weeks of TAU. Patients randomized to TAU will start with CPAP treatment after the four-week intervention period. Neuropsychological assessment and examination of functional status, the primary outcome measures, are conducted at baseline and repeated after the four-week intervention period and at two-month follow-up. The secondary measures sleep quality, fatigue, and mood are assessed at the same time points as the primary outcome measures. To ascertain whether OSA improves with CPAP treatment, direct measurements of OSA, including AHI and level of oxygen desaturation during sleep, are made at baseline, at the end of the intervention period, and at two-month follow-up. To assess treatment compliance, the CPAP device registers CPAP usage per night, the air pressure and the residual AHI. At four weeks, and three, six and twelve months after enrollment the rehabilitation physician checks the compliance.

To test the hypothesis of the case–control study that OSA is associated with poor functional status and greater cognitive impairment, 70 stroke patients diagnosed with OSA are compared to 70 stroke patients without OSA on the primary and secondary outcomes at admission to the rehabilitation unit (baseline).

In a subgroup of the stroke patients without OSA (N = 35) the assessment of primary and secondary outcome measures will be repeated after four weeks and three months. The outcomes will be compared to the recovery of OSA patients.

All patients included in the TOROS study are asked to fill out a questionnaire on participation in work, leisure and social activities at six months and one year after inclusion. The study design is illustrated in Figure 1.

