### Statistical analyses

All statistical analyses will be performed with SPSS 19 (IBM; Armonck, USA) or later versions of this package. Depending on the level of measurement, parametric statistics (Student’s *t*-test and analysis of (co)variance) or non-parametric statistics (*χ*^2^ and Fisher’s exact test) will be used. Statistical significance will be set at a p-value of 0.05 or less. Socio-demographic and clinical characteristics at baseline will be presented using descriptive statistics. If group differences are observed at baseline on one or more background variables, those variables will be included as covariates in all further analyses.

For the RCT, the therapy effects on the primary and secondary outcome measures will be examined using a two factor (group × time) multivariate analysis of variance (MANOVA). Effect sizes will be calculated for all analyses using standard statistical procedures. To control for the multiple comparisons of cognition and functional status, two separate MANOVA’s will be performed. Given that we have two primary outcomes defined for the study (i.e., cognitive and functional outcomes), we will subsequently follow Hochberg’s step-up procedure [36] to control the false discovery rate.

Data will be analyzed according to the intention-to-treat principle. Additionally, a per-protocol analysis will be performed. Depending on the variability of compliance, a secondary analysis of good versus poor compliance will be conducted. In an exploratory analysis, we will investigate whether the effectiveness of CPAP therapy varies as a function of clinical diagnosis, level of cognitive functioning, and demographic background.

For the supplementary case–control part of the study, OSA patients will be compared with the control group of non-OSA patients on primary and secondary outcome measures using a MANOVA. As with the RCT, a separate analysis will be performed for cognition and functional status, and the Hochberg’s step-up procedure will be followed. For the follow-up of the USER-P questionnaire, within group changes will be assessed using paired t-tests and between group comparison will be made with two sample *t*-test.

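### Change in AHI and CPAP compliance arise after randomization, so they cannot serve as moderators, and the good-versus-poor compliance contrast is non-randomized and open to bias

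*Protocol article*

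**What the plan says.** Under Secondary outcomes the protocol article names two moderators for the RCT: "The change of AHI measured by polygraphy and treatment compliance are used as moderating variables in the RCT". Statistical analyses adds: "Depending on the variability of compliance, a secondary analysis of good versus poor compliance will be conducted".

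The timing and source of the two variables are given elsewhere:

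- Randomization and blinding: "Participants with OSA will be randomized immediately after the baseline assessments".
- Design, on the AHI and desaturation recordings: they "are made at baseline, at the end of the intervention period, and at two-month follow-up". Their declared purpose is to see whether OSA improves under CPAP.
- Design, on compliance: "the CPAP device registers CPAP usage per night, the air pressure and the residual AHI".
- Design, on the control arm: "Patients randomized to TAU will start with CPAP treatment after the four-week intervention period".

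The governing principle is "Data will be analyzed according to the intention-to-treat principle", followed by "Additionally, a per-protocol analysis will be performed". A separate exploratory analysis looks at whether the CPAP effect differs by clinical diagnosis, cognitive level and demographic background.

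**The concern.** A moderator is a characteristic that treatment cannot have altered, across whose levels the randomized effect is compared. Neither named variable qualifies. CPAP is meant to lower AHI, so grouping patients by change in AHI conditions on part of what the treatment does. Compliance is behaviour after assignment and is recorded in only one arm during the randomized period. Patients who use the device well may differ in prognosis from those who do not, and randomization gives no protection against that difference.

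What is at stake is the reading of the secondary results. A difference between good and poor compliers could be taken as evidence that CPAP helps when it reflects only who manages to comply. The plan expects compliance of around 67%, so roughly a third of the CPAP arm could fall in the poor group.

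**Working it through.** **1. When each variable arises.** Randomization follows directly on the baseline assessments. Change in AHI needs a later recording, at the end of the intervention or at two-month follow-up. Compliance needs nights on the device. Both therefore arise after randomization.

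**2. Change in AHI as the target of treatment.** Entry to the RCT requires AHI of at least 15. Under Intervention, pressure is adjusted until the ODI is below 5 or, if that fails by oximetry, towards an AHI below 5 or the highest tolerated pressure. A CPAP patient who reaches an AHI below 5 has dropped by more than 15 − 5 = 10 events per hour. TAU patients get no CPAP in those weeks. Change in AHI is thus expected to separate the arms by design. Among well-treated patients it also lies close to baseline AHI, so it mixes response with OSA severity.

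**3. Compliance in the TAU arm.** The device is the source, and TAU patients start CPAP only after week 4. Over the randomized period compliance is undefined in one arm, so the treatment effect cannot be compared across compliance levels. After week 4 TAU patients may have values, but the arms no longer contrast CPAP with no CPAP.

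**4. Size of a spurious good-versus-poor difference.** The plan states no figure to reproduce, so this is an illustration.

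Inputs: 35 patients in the CPAP arm (Abstract); proportion of good compliers p = 0.67 (Sample size), about 35 × 0.67 = 23 patients; true CPAP effect zero. The correlation r between the tendency to comply and the outcome without treatment is an assumption, varied from 0 to 0.5. The contrast is taken within the CPAP arm, which is also an assumption because the article does not say how it is built.

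With a normal tendency to comply, cut so that a fraction p are good compliers, the expected difference in SD units is

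r × φ(q) / [p(1 − p)], where q is the 33rd percentile of the standard normal.

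Here q = −0.44, φ(q) = 0.362 and p(1 − p) = 0.67 × 0.33 = 0.221, so the multiplier is 0.362 / 0.221 = 1.64. At r = 0.5 this gives 0.82 SD.

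A simulation of 20,000 trials agrees. The false-positive rate is for a t-test at a nominal two-sided 5%.

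| Assumed r | Mean good-minus-poor difference (SD) | False-positive rate |
|---|---|---|
| 0 | 0.00 | 5% |
| 0.1 | 0.16 | 7% |
| 0.2 | 0.33 | 15% |
| 0.3 | 0.49 | 26% |
| 0.4 | 0.65 | 45% |
| 0.5 | 0.82 | 66% |

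The intention-to-treat difference averaged about zero in every row. For scale, the plan sizes the cognitive outcome on 0.75 SD; at r of 0.4 to 0.5 the spurious contrast is of that order. A negative r would reverse the sign.

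**The case against.** The strongest reply is that nothing here touches the main inference. Intention to treat governs, neither variable is named in the group × time MANOVA, and the compliance comparison is called secondary. That stands in full. Several stronger readings are tempting, and the document does not support them:

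- *That the plan will fit a group × compliance term, or adjust the treatment effect for change in AHI.* No such model is written down. An article may leave model form to the full protocol. What is stated is the moderator role, and that is wrong whatever the model.
- *That the secondary analyses will give biased answers.* No passage links compliance to prognosis. At r = 0 the contrast is unbiased; size and direction are unknown.
- *That these analyses are meant to show whether CPAP works when used, or will carry the interpretation.* The article says neither. The 67% appears only in setting the sample size.
- *That the conditional wording permits results-driven selection.* The condition is the spread of compliance, not the outcome. If nearly everyone complies, the comparison is not feasible. This is a feasibility condition.
- *That the per-protocol analysis carries a calculable bias.* Its analysis set is not defined in the article, so no figure can be attached to it.

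It is also fair that part of the remedy is already planned: AHI is recorded before and after treatment to see whether OSA improves, OSA severity is a minimization factor, and effect modification by pre-treatment characteristics is explored separately. This shortens the repair. It does not make the sentence on moderators correct.

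**Conclusion.** The point holds as a fault in stated secondary analyses. Change in AHI is a potential mediator. Compliance is a post-randomization variable with no value in TAU over the four randomized weeks. Neither can be read as effect modification, and the good-versus-poor contrast is not protected by randomization. It is open to bias unless compliance and AHI response are unrelated to prognosis, which the article does not argue.

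With zero CPAP effect, the illustrative good-minus-poor difference is 0 to about 0.8 SD for r from 0 to 0.5. This range rests on the assumed r, on 67% good compliers and on a contrast within the CPAP arm. It shows what is possible and is not a forecast. A reader might infer that the primary result is compromised; it is not, because the intention-to-treat comparison does not use either variable.

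**What to change.** 1. Restrict moderators to variables measured before randomization, and use baseline AHI in place of change in AHI.
2. Report change in AHI by arm as a measure of treatment delivery, or in a mediation analysis labelled exploratory with its assumptions stated.
3. Label the good-versus-poor comparison as non-randomized and descriptive, and adjust it for baseline prognostic variables.
4. Optionally, add a week-4 instrumental-variable (complier-average) estimate with randomized arm as the instrument. Hours of CPAP use are preferable to a compliance cut-off. State the exclusion restriction: assignment affects outcome only through CPAP use as modelled. The estimate should stop at week 4, since TAU patients then start CPAP.

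Items 1 to 3 cost wording and use data already planned. Item 4 costs one further regression and has real drawbacks. With a cut-off and 67% compliance the interval is about 1/0.67 = 1.5 times as wide as the intention-to-treat interval. The estimate may also be inflated if patients below the cut-off benefit from partial use. Contact with the Respicare team could do the same, since the comparison is with TAU and not sham.

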### Sample size

We conducted two separate power analyses for the RCT; one for the functional outcome and one for the cognitive outcome. The power calculation for the functional outcome is based on two previous studies [18,19]. These studies found large effects of CPAP treatment on functional outcome measures in stroke patients. To detect at least one standard deviation (large effect) on functional outcome with 90% power and an alpha of 0.05 (one-tailed), a minimum of 34 patients (17 per arm) is required.

No reliable information on the expected effect of CPAP treatment on cognitive measures is available. Therefore, an effect size of 0.75 standard deviation was used to estimate the necessary sample size. Taken the same alpha level and 80% power, a minimum of 56 patients (28 per arm) needs to be included in the RCT. The compliance in this study is expected to be relatively high (around 67%) due to the relatively short duration of the experimental treatment phase and the assistance of a specially trained staff. Taking the compliance rate into account, a total of 70 patients will be the target sample size for the RCT.

For the supplementary case–control study, we set the sample size at 70 OSA patients and 70 patients without OSA, which allows detection of a medium size effect (0.5 standard deviation) with 90% power, and p-value set at 0.5.

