**Methods/Design:**

A randomized controlled trial will be conducted on the neurorehabilitation unit of Heliomare, a rehabilitation center in the Netherlands. Seventy stroke patients with obstructive sleep apnea will be randomly allocated to an intervention or control group (n = 2×35). The intervention will consist of four weeks of continuous positive airway pressure treatment. Patients allocated to the control group will receive four weeks of treatment as usual. Outcomes will be assessed at baseline, immediately after the intervention and at two-month follow-up.

In a supplementary study, these 70 patients with obstructive sleep apnea will be compared to 70 stroke patients without obstructive sleep apnea with respect to cognitive and functional status at rehabilitation admission. Additionally, the societal participation of both groups will be assessed at six months and one year after inclusion.

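### The two RCT sample-size figures use different sidedness under one alpha label, and neither is the power of the planned MANOVA

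*Protocol article*

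**What the plan says.** Protocol article, Sample size. The functional calculation targets a difference of 1.0 SD: "with 90% power and an alpha of 0.05 (one-tailed), a minimum of 34 patients (17 per arm) is required". For cognition, "an effect size of 0.75 standard deviation was used to estimate the necessary sample size", and then: "Taken the same alpha level and 80% power, a minimum of 56 patients (28 per arm) needs to be included in the RCT". The only alpha stated before that sentence is the one-tailed 0.05. The target of 70 patients follows after an allowance for compliance; the abstract gives the split as 35 per arm.

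Protocol article, Primary outcomes. "The following nine cognition domains are assessed", each as a demographically corrected z-score (averaged where a domain has several tests). No overall cognitive score is defined.

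Protocol article, Statistical analyses. Treatment effects are examined by a group × time MANOVA. "To control for the multiple comparisons of cognition and functional status, two separate MANOVA’s will be performed", followed by Hochberg's procedure across the two outcomes. Significance is set at p of 0.05 or less, with no mention of one-tailed testing.

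**The concern.** There are two separate faults.

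- **Sidedness.** Someone who takes the section at its word and recalculates the cognitive sample size at one-tailed 0.05 does not get 28 per arm. Someone who assumes two-sided testing throughout gets 28 but then does not get 17 for function. The reader cannot tell which error rate the trial was designed around.
- **Matching the test.** A power statement is useful only if it describes the test that will be run. Both calculations concern one standardised difference on one outcome. The cognitive test is an omnibus F-test on nine variables, which has no one-tailed form and whose power depends on how many domains move and how they correlate. The article ties the 0.75 SD to no domain, summary score or multivariate distance, so the 80% cannot be read as the power of the primary cognitive analysis.

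At stake is how a null cognitive result is read. If it is reported as coming from a trial with 80% power, that figure belongs to a different test.

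**Working it through.** **Inputs from the article:** functional effect 1.0 SD, 90% power, alpha 0.05 one-tailed, 17 per arm; cognitive effect 0.75 SD, 80% power, same alpha, 28 per arm; equal allocation, 35 per arm planned; nine cognitive domains.

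**Step 1. The plan's own figures.** Normal approximation: n per arm = 2(z_alpha + z_power)² / d². Here z = 1.645 (one-tailed) or 1.960 (two-sided) for alpha 0.05, 1.282 for 90% power and 0.842 for 80%.

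- Functional, one-tailed: 2(1.645 + 1.282)² / 1² = 17.1
- Functional, two-sided: 2(1.960 + 1.282)² / 1² = 21.0
- Cognitive, one-tailed: 2(1.645 + 0.842)² / 0.5625 = 22.0
- Cognitive, two-sided: 2(1.960 + 0.842)² / 0.5625 = 27.9

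The same with the noncentral t distribution:

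| Outcome | Stated per arm | Needed, one-tailed | Needed, two-sided | Power at stated n, one-tailed | Power at stated n, two-sided |
|---|---|---|---|---|---|
| Functional, 1.0 SD, 90% | 17 | 17.8 | 22.0 | 88.6% | 81% |
| Cognitive, 0.75 SD, 80% | 28 | 22.7 | 28.9 | 87% | 79% |

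The functional 17 comes from the one-tailed formula, rounded down (18 gives 90.2%). The cognitive 28 comes from the two-sided formula.

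**Step 2. Alternative readings.** If the carried-over alpha means only the value 0.05, 28 is right as a two-sided number, but the functional figure then uses a different sidedness without saying so. One-tailed 0.025 would also give 28, but the text does not state it.

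**Step 3. Power of a nine-variable test (illustration).** Assumptions, because the article gives none of these: a single group contrast tested by Hotelling's T², every pair of domains correlated r, k of the nine domains shifting by 0.75 SD and the rest not at all, complete data and full compliance, alpha 0.05.

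Multivariate distance: Δ² = [0.5625 / (1 − r)] × [k − r k² / (1 + 8r)]. Noncentrality: (n/2)Δ². F degrees of freedom: 9 and 2n − 10.

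Example, k = 1, r = 0, n = 35: Δ² = 0.5625, noncentrality 17.5 × 0.5625 = 9.84, F on 9 and 60 df, power 49%.

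| Domains shifting 0.75 SD | n per arm | r = 0 | r = 0.3 | r = 0.5 | r = 0.7 |
|---|---|---|---|---|---|
| One | 28 | 38% | 49% | 66% | 90% |
| One | 35 | 49% | 62% | 79% | 97% |
| Two | 35 | 84% | 91% | 98% | over 99% |
| All nine | 28 | about 100% | 85% | 66% | 51% |
| All nine | 35 | about 100% | 94% | 79% | 65% |

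The single-outcome 80% therefore does not carry over, and the difference can go either way.

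**The case against.** **The sidedness slip costs nothing.** The cognitive figure sets the target and is larger than its label requires (28 against 22-23). The functional shortfall, 17 against 17.1, is rounding, and 35 per arm covers it. This stands: it is a fault of statement, and that step did not make the trial too small.

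**Powering on a simple univariate effect is common,** especially where, as here, the authors say they have no reliable effect estimate for cognition. That is fair as a planning device. It does not make the 80% a property of the MANOVA, and the article does not say that it is only a planning figure.

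**The MANOVA numbers rest on undocumented inputs.** Correct. The article gives no correlations or effect pattern, and the planned group × time test over repeated assessments is not a single-contrast Hotelling test. The table shows dependence; it does not estimate the trial's power.

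Three stronger readings are tempting, and the documents do not support them:

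- *That the cognitive analysis is underpowered, or reaches 80% only if every domain shifts by about 0.75 SD.* In the illustration two shifted domains give 84% or more at 35 per arm, while all nine shifting at r = 0.7 give 65%. A shift in every domain is neither necessary nor sufficient.
- *That a non-directional test cannot serve an objective about improvement.* Reading direction from the estimates after a two-sided test is ordinary practice. The article plans effect sizes for all analyses, and how domain results follow a significant MANOVA is detail that the full protocol or SAP may hold.
- *That the mean of the nine domains ought to replace the MANOVA.* That is a trade-off. At r = 0.3 and 35 per arm, a shift in one, two or three domains gives the mean score 9%, 20% and 39% power, against 62%, 91% and 97-98% for the nine-variable test. The mean score does better when all domains move together (r = 0.5: 99% against 79%). The article's Background points to effects in particular domains such as attention.

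**Conclusion.** The concern holds in a limited form. As written, the Sample size section is internally inconsistent: 17 per arm is a one-tailed figure and 28 per arm a two-sided one, under a single alpha label. This conclusion uses only the article's own inputs. For cognition the error is conservative by 5-6 patients per arm.

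The stated power is also not the power of the planned analysis, because a univariate calculation (one-tailed for function) is set against a non-directional multivariate test. That mismatch follows from the text. Its size does not: under the assumptions above, cognitive power at 35 per arm ranges from 49% to about 100%, so no fixed claim of too little or ample power is justified.

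**What to change.** - Restate both calculations at two-sided 0.05: functional, 1.0 SD and 90% power, 22-23 per arm; cognitive, 0.75 SD and 80% power, 28-29 per arm. Both fit within 35 per arm before any loss to non-compliance.
- Say which cognitive quantity the 0.75 SD refers to: a named domain, a summary score or a multivariate distance.
- Then either label the 80% as the power of a single-outcome comparison, or give the MANOVA's own power for the planned group × time test under stated domain effects and correlations, with a range.

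The first two changes and the labelling option are wording only. The MANOVA option needs one further calculation and an explicit assumption about correlations. None of these restatements adds patients or changes the test. A move to a mean-of-domains confirmatory score is optional; if it is considered, its loss of power for effects confined to a few domains should be set out.
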